### Participants

Youth participants will be of AI ethnicity, ages 11 to 19 and have primary residence on or near the participating tribal reservation community. Parent/trusted adult participants will be chosen by the youth and be the parent/legal guardian of the participating youth or another family member or trusted adult over the age of 18. If the youth choses an adult who is not the legal guardian, the adult must be approved by the legal guardian. Participants who are unable to fully participate in the evaluation assessments or intervention components will be excluded (see Table 1 for Inclusion and Exclusion criteria). All participants will complete informed consent to participate; youth under age 18 will have parent/guardian consent.

**Table 1 Tab1:** Inclusion and exclusion criteria

Inclusion criteria		
	Youth	-Self-identified American Indian -11-19 years old -Primary residence on or near the reservation -Written informed consent (parent/guardian consent if 11–17 years old)
	Parent/trusted adult	-Parent, legal guardian or trusted adult -18 years old or older -Primary residence on or near the reservation -Written informed consent
Exclusion criteria		
	Youth	-Unwilling to be randomized -Unable to complete intervention because of cognitive limitations -Unable to complete evaluation (i.e., planned move, residential treatment, etc.)
	Parent/trusted adult	-Unwilling to be randomized -Unable to complete intervention because of cognitive limitations -Unable to complete evaluation (i.e., planned move, residential treatment, etc.)

We will use non-probability sampling to recruit participants through public postings in community gathering spots (i.e., supermarket, daycares, fitness center, etc.), through public service announcements on the local radio, by print advertising in the local newspaper, during public gatherings (i.e., health fairs, parades, etc.) and through local schools. We will recruit three cohorts of participants and host three summer basketball camps (2016, 2017 and 2018).

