### Randomization

Participants will be individually randomized to receive the intervention or control program. Participants will be assigned to either program through a stratified block randomization sequence using Stata 14 [24] to ensure a 1:1 allocation of study conditions occurs within each gender and age sub-group (11–12, 13–15 and 16–19). Since both the RCL and control program include a youth-parent component, siblings will be randomized to the same group.

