This sample size will also be able to detect meaningful differences between the intervention and control groups with at least 80% power, given the assumptions listed above: 6.7% between-group difference in reproductive/sexual health knowledge score [estimating a mean score (SD) of 76% (16%) in the control group] and 20.5% between-group difference in intention to use a condom at next sex (estimating 55% in the control group).

Study hypotheses will be initially tested under an “intent-to-treat” model in which data are analyzed according to randomization assignment. We will then conduct “completer analyses” on those subjects finishing at least two-thirds of the 9 intervention sessions. Intervention impact will be evaluated by comparing primary study outcomes between intervention and control groups across the three time points: baseline, 3 and 9 months post-intervention. Initially, summary scores of outcomes will be stratified by participation in the intervention versus control groups and by time point and compared using chi-square tests (for binary or categorical outcomes), t-tests and analysis of variance (for continuous outcomes). The equivalence of the two study groups at baseline will be compared across a range of background variables. Generalized linear mixed effects models (GLMMs) accounting for within-group correlation across longitudinal data will then be applied.

Outcomes will be modeled as a function of group assignment and time since intervention. The association between outcomes and time will be explored visually using scatterplots and lowess smoothers. Restricted cubic splines will be added to reflect deviations from linearity. GLMM with random intercepts for peer group and study participant will be used to account for the hierarchical structure of the data: peer group, participants nested within peer group and assessments nested within study participants. If siblings enter the study together during the same wave, they will be randomized to the same study group (intervention or control) to limit contamination. In this case, analyses will be adjusted to take into account intra-sibling correlation as well. Missing data will be handled as follows: (1) document reason(s) for missing data to inform model development; (2) assess treatment dropouts to do intent-to-treat analysis; (3) conduct sensitivity analysis to compare inferences that are based on different plausible reasons for missingness [32, 33].

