### Methods Against Bias

Separate cadres of research staff will be hired and trained as RCL or control facilitators and independent evaluators. Facilitators will be responsible for delivering either the RCL or control program and will not participate in any aspect of the evaluation. Independent evaluators will conduct screening for inclusion and exclusion criteria, obtain informed consent, enroll eligible youth and parents/trusted adults, and administer all evaluations to youth and parents. Independent evaluators will not participate in any aspect of RCL or control program delivery. All research staff are members of the participating tribal community and employed/trained by the academic research partner. Research staff complete a background check and are extensively trained in human subject’s research prior to any interaction with participants or study data.

To ensure the RCL and control programs are implemented in a comparable way, all facilitators will receive extensive training in their respective program and must pass a proficiency examination with a score ≥85% prior to delivery. In addition, fidelity monitoring of RCL and control program implementation will be performed on ≥10% of all sessions conducted. Sessions will be randomly selected and observed in person, audio recorded or video recorded. Staff performing fidelity monitoring will complete a feedback form and review it with the RCL or control facilitator. Additional training will be conducted as necessary.

To reduce potential for contamination across study groups, RCL and control programs are delivered in separate camp locations. Youth in each group participate in basketball play only with other youth receiving the same program (RCL or control). All staff members, including basketball coaches, are instructed not to discuss the content of either program outside of the classroom. Siblings will also be randomized to the same group (RCL or control) to avoid contamination within families.

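### The sibling allocation rule is unconditional in two sections but limited to same-wave siblings in a third, and the correlation adjustment omits siblings who enter in different waves

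*Protocol article*

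**What the plan says.** All of this is in the protocol article.

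- **Randomization** gives the rule without a wave condition and ties it to the youth-parent lesson: "Since both the RCL and control program include a youth-parent component, siblings will be randomized to the same group".
- **Methods Against Bias** repeats it without condition and lists it as a safeguard: "Siblings will also be randomized to the same group (RCL or control) to avoid contamination within families".
- **Sample Size Calculation and Statistical Analysis** adds a condition: "If siblings enter the study together during the same wave, they will be randomized to the same study group". The sentence after it reads: "In this case, analyses will be adjusted to take into account intra-sibling correlation as well".
- The same section sets out the model: "GLMM with random intercepts for peer group and study participant will be used to account for the hierarchical structure of the data". No family term is named apart from the same-wave adjustment.
- **Participants** shows that the uncovered case can arise. There are three yearly cohorts ("We will recruit three cohorts of participants and host three summer basketball camps (2016, 2017 and 2018") and a wide age range ("Youth participants will be of AI ethnicity, ages 11 to 19").

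No section says how a youth is allocated or modelled when a sibling took part in an earlier camp.

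**The concern.** For a youth whose sibling attended an earlier camp, two sections require the sibling's arm and the third leaves the youth outside the rule. Staff enrolling a returning family could follow either text.

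What is at stake depends on which text is followed:

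- **Siblings share an arm.** Their outcomes are probably positively correlated, and the adjustment as worded does not reach them. Standard errors come out slightly too small.
- **Siblings are split.** One household, possibly through the same chosen adult, can receive both programmes. That is the within-family contamination that Methods Against Bias says is prevented, and it would pull the arms together.

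These are alternatives and do not add up for the same pair of siblings.

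**Working it through.** **1. The texts side by side**

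| Section | Siblings in the same wave | Siblings in different waves |
|---|---|---|
| Randomization | same arm | same arm |
| Methods Against Bias | same arm | same arm |
| Statistical Analysis, allocation | same arm | not addressed |
| Statistical Analysis, adjustment | included | not included |

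Siblings from different camps are in different peer groups and are different participants. Neither stated random intercept links them, so the model treats them as independent under either allocation rule.

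**2. Inputs from the sample size section**

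Significance level 0.0125 (taken as two-sided; the article does not say), power 90%, difference 0.47, SD 1.0, intra-team correlation 0.12, team size after loss 7.2.

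- Normal quantiles: 2.498 for the test and 1.282 for power; sum 3.779.
- Team design effect, reading 0.12 as an intra-class correlation: 1 + (7.2 − 1) × 0.12 = 1.744.

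*Check on the stated ~32 teams per arm.* Without averaging the two follow-up measures, 2 × 3.779² / 0.47² gives 130 per arm, and 130 × 1.744 / 7.2 = 31.5, so 32 teams. With averaging (variance 0.85) the same formula gives 110 × 1.744 / 7.2 = 26.6, so 27. The Hayes–Bennett formula, with 0.12 as a coefficient of variation and averaging, gives 30.3 + 1 = 31.3, so 32. The stated figure is reachable and is not disputed. None of these calculations has a sibling term.

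**3. Assumptions, not given in the article**

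Share of youth with one cross-wave sibling, f = 10–30%. Sibling correlation, ρ = 0.2–0.4. The product fρ runs from 0.10 × 0.2 = 0.02 to 0.30 × 0.4 = 0.12.

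**4. Siblings share an arm, correlation ignored**

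True variance relative to modelled variance = (1.744 + fρ) / 1.744. True error rate = 2 × [1 − Φ(2.498 / √ratio)].

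| fρ | Variance ratio | True error rate |
|---|---|---|
| 0.02 | 1.764 / 1.744 = 1.011 | 0.0130 |
| 0.12 | 1.864 / 1.744 = 1.069 | 0.0157 |

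If 0.12 is instead a coefficient of variation, the between-team variance is 0.12² × 2.6² = 0.0973 and the design effect is 1 + 6.2 × 0.0973 = 1.604. The upper end then becomes 1.724 / 1.604 = 1.075 and 0.0160, so the reading hardly matters.

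**5. Siblings split, correlation ignored**

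The sign reverses: (1.744 − fρ) / 1.744 = 0.989 to 0.931, and the true error rate is 0.0120 to 0.0096. The test is conservative.

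**6. Siblings split, contamination**

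The last lesson falls within 3 months of camp and the primary follow-up ends 9 months after completion. A youth's primary follow-up is therefore over at about the time of the next yearly camp. For the 9-month endpoint, contamination runs essentially from an earlier RCL sibling to a later control sibling. Among controls with a cross-wave sibling, half are the later entrant, and under independent 1:1 allocation half of those have an RCL sibling, which is one quarter.

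- Exposed controls: 10% × 1/4 = 2.5% to 30% × 1/4 = 7.5%.
- With half the effect carried over (assumed): 0.47 × (1 − 0.0125) = 0.464 to 0.47 × (1 − 0.0375) = 0.452.
- Power: Φ(3.779 × 0.9875 − 2.498) = 89% to Φ(3.779 × 0.9625 − 2.498) = 87%.

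**The case against.** The strongest reply is that the statistical section may simply restate the general rule for the commonest situation. It is silent on cross-wave siblings, while the other two sections, read literally, already cover them. On that view no family is split and only the wording needs tidying.

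Part of this stands. A reader might infer that the protocol plans to randomise cross-wave siblings independently. The text does not say so: it leaves the case open, and a split is permitted by one section and excluded by two. It also gives no sibling frequency, so cross-wave siblings are possible but their number is unknown.

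A reader might also infer larger effects:

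- Taking 1 + fρ as the whole design effect gives 1.02–1.12 and an error rate up to 0.018. That ignores the team clustering the plan already allows for.
- Treating 10% of controls as exposed gives power of 86%. By the one-quarter argument, that needs a cross-wave share of 10% / 0.25 = 40%, above the assumed range.
- Omitting the correlation does not always make the test too liberal. If siblings are split it makes it conservative.

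Extended follow-up to 12–36 months would lengthen exposure, but it depends on funding not yet secured.

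The reply does not remove the conflict. Even if the unconditional rule governs allocation, the adjustment sentence still covers only same-wave siblings.

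**Conclusion.** The point holds as an inconsistency in the allocation rule together with a gap in the analysis rule. Nothing else in the article reconciles the three statements. The gap in the model remains whichever allocation rule is meant.

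The numerical effect is small. With siblings in the same arm, the true variance exceeds the modelled variance by about 1–7%, and the error rate is about 0.0130–0.0157 in place of 0.0125. With siblings split, the analysis is conservative, and contamination costs about one to three percentage points of power. These figures rest on an assumed sibling share, sibling correlation and half carry-over, none of which the article gives. They do not show that a trial conclusion would change. The case for acting is that recruitment is open, the rule must be applied at enrolment, and the repair is cheap.

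**What to change.** 1. State one sibling rule, worded identically in Randomization, Sample Size Calculation and Statistical Analysis, and Methods Against Bias, and make it cover siblings entering in different waves. If later siblings take the first sibling's arm, say how this fits the gender-by-age stratified blocks and acknowledge that their arm is then known in advance.
2. Record at enrolment a family identifier and the arm of any sibling who took part earlier.
3. Remove the opening condition from the adjustment sentence, and include a family random effect, crossed with peer group, for all enrolled siblings whatever their wave.
4. Only if the chosen rule allows siblings to be split, add a sensitivity analysis excluding later-wave youth whose household had already received the other programme. Under a same-arm rule this analysis would be empty.

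The cost is some wording, two data items and a slightly more complex model. Family must be crossed with peer group because siblings of different sex or from different camps are in different groups. Many families may contribute one child, so the family variance may be poorly estimated.

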### Methods Against Bias

Separate cadres of research staff will be hired and trained as RCL or control facilitators and independent evaluators. Facilitators will be responsible for delivering either the RCL or control program and will not participate in any aspect of the evaluation. Independent evaluators will conduct screening for inclusion and exclusion criteria, obtain informed consent, enroll eligible youth and parents/trusted adults, and administer all evaluations to youth and parents. Independent evaluators will not participate in any aspect of RCL or control program delivery. All research staff are members of the participating tribal community and employed/trained by the academic research partner. Research staff complete a background check and are extensively trained in human subject’s research prior to any interaction with participants or study data.

To ensure the RCL and control programs are implemented in a comparable way, all facilitators will receive extensive training in their respective program and must pass a proficiency examination with a score ≥85% prior to delivery. In addition, fidelity monitoring of RCL and control program implementation will be performed on ≥10% of all sessions conducted. Sessions will be randomly selected and observed in person, audio recorded or video recorded. Staff performing fidelity monitoring will complete a feedback form and review it with the RCL or control facilitator. Additional training will be conducted as necessary.

To reduce potential for contamination across study groups, RCL and control programs are delivered in separate camp locations. Youth in each group participate in basketball play only with other youth receiving the same program (RCL or control). All staff members, including basketball coaches, are instructed not to discuss the content of either program outside of the classroom. Siblings will also be randomized to the same group (RCL or control) to avoid contamination within families.

Data quality and maintenance of confidentiality are continuously monitored by the principal investigator. A unique participant ID code will be used to administer and track all data collection, stored separately from data collection tools and locked in a secure room with limited access by authorized individuals. Data will be stored in a database that is password protected and located on a secure server. Only the personal identifier of participants’ date of birth will be included in the database. Any electronic documents that link IDs to identifying information (i.e., names/signatures on consent forms and logs) will be stored in accordance with the academic partner’s data security guidance. Transfer or storage of data on portable devices (e.g., laptops, flashdrives) will be encrypted and accessible only to study personnel.

### Safety and Ethical Issues

This trial has received approval from the funding agency and relevant Indian Health Service and University research review boards. Any necessary protocol modifications will be submitted as amendments for review to these relevant parties. The trial and manuscript were approved by the participating tribal community’s governing bodies. Independent evaluators will obtain informed written consent from all adult participants and assent and parental permission from all minor participants (<18 years of age). Independent evaluators will explain the study including procedures, risks and benefits associated with participating, and the rights and responsibilities of study participants. Staff will encourage participants to ask questions and provide copies of the consent form. Participants will be informed that they can stop study participation at any time. The Principal investigator has obtained a Certificate of Confidentiality from the Department of Health and Human Services, which states researchers cannot be forced to disclose information that may identify participants, even by court subpoena, in any federal, state or local civil, criminal, administrative, legislative or other proceedings. Any serious adverse event reported or detected during the trial will be documented and reported to the relevant research review boards within 24 h. There is no Data and Safety Monitoring Board for this trial. [Note: a completed SPIRIT checklist (Additional file 1) was submitted along with the manuscript to the journal].

## Discussion

The RCL intervention is ground-breaking in that it successfully promotes concentric circles of support for adolescents’ positive behavior change at individual, peer, family and community levels. Intergenerational intervention has special import to AI communities as family is generally valued as the nexus of strength for individuals and been shown to yield great influence on adolescents’ behavioral choices [34–36]. Also, historical and present-day trauma have eroded traditional family structures (i.e., poverty and overcrowded households, single parent homes, high residential mobility) and contributed to intergenerational cycles of teen pregnancy. Native families experiencing these stressors may rely on a combination of immediate and extended family members as well as close friends for caretaking [37]. Native parents and communities are eager for prevention interventions that strengthen entire family networks; thus, incorporation of parents or trusted adults in the RCL program is socially and culturally congruent for AI youth and families and holds promise for reducing accumulated risk across generations [37].

Currently there are no interventions for the prevention of STIs, HIV and teen pregnancy designed specifically for American Indian youth that have been rigorously evaluated and found to have an evidence-base. RCL is highly innovative as it: (1) incorporates a summer basketball camp and home visits, (2) fills health education gaps in rural, reservation-based communities, (3) targets males and females equally, both key to the prevention equation, (4) acknowledges the inextricable link between substance use and unintended pregnancy and (5) addresses intergenerational cycles of teen pregnancy in communities experiencing the repercussions of historical and modern day trauma. If RCL is found successful, it will be the first evidence-based program for teen pregnancy prevention among American Indian youth and adolescents.

### Trial status

Youth and parents began to enter the trial in May 2016. Recruitment is still open.

## Abbreviations

ACASI: Audio Computer Assisted Self-Interview
AI: American Indian
AI/AN: American Indian/Alaska Native
CAB: Community Advisory Board
EBI: Evidence-based intervention
FOY: Focus on Youth
GLMM: Generalized Linear Mixed Effects Models
ImPACT: Informed Parents and Children Together
RCL: Respecting the Circle of Life
RCT: Randomized Controlled Trial
YHRBI: Youth Health Risk Behavioral Inventory
